### Statistics

Sample size

Our main goal is to estimate the proportion of patients showing severe hypotension and, notably, to corroborate the prevalence found in Liem
*et al.*
^
5
^
*i.e.*, 8%. To gain a 10% precision (± 5%) with a two-sided 5% alpha risk, 114 patients need to be included.

Detection of artefacts

This will follow similar rules as previously published in a paper dedicated to the validation a new sensor.
^
14
^ The rules selected to define artefacts may be updated according to experience and the literature.
^
15
^ The successive rules will be recorded in a register, and all recordings will be reviewed in the light of these new rules.

Missing values

Missing data will not be replaced.

Statistical analyses

Descriptive summaries will be provided for each parameter and for each device. For continuous variables, the mean, median, and their 95% confidence limits, obtained using bootstrapping methods, will be provided. For discrete variables, counts, percentages, and confidence limits obtained using a bootstrap method will be provided
*.*

The proportion of data gaps and artefacts for each parameter will be given as a percentage of the total number of measurement points and observations, respectively, with the corresponding 95% confidence interval (CI).

When physiologic parameters (HR, SAP, DAP, for instance) are measured simultaneously by nurses and wearable devices, a Bland-Altman analysis for repeated measurements, accounting for multiple observations per individual, will be performed to draw mean-difference plots and derive accuracy or bias (mean difference), precision (standard deviation of difference), and limits of agreement (LoAs) that are expected to contain 95% of the paired differences between measurements by the nurses and the wireless patch, with their confidence intervals.

At the patient level and for each kind of clinical event, the proportion of patients with detection of at least one event (hypotension, for instance) by a nurse and wearable monitoring will be described in a two-by-two table. Agreement will be estimated by Cohen’s kappa coefficient with its 95% CI, while differences will be tested by a non-parametric McNemar test for paired nominal data.

The time (hours) to first occurrence of data loss or end of service of the device, or to the first occurrence of a clinical complication, will be described with Kaplan-Meier survival curves, and, if permitted by the number of such events, risk factors will be explored by a Cox model.

Interim analyses are not planned in this study.

A two-tailed p value < 0.05 will be considered statistically significant. All statistical analyses will be performed using R software (R Development Core Team, 2012.
https://www.r-project.org/).

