### Data collection

Demographic data, including age, sex, American Society of Anesthesiologists classification, body mass index, underlying diseases, type and duration of the surgical procedure, and type of surgical procedure, will be collected upon inclusion in the study. Postoperative medications including opioids and other analgesics will also be collected.

All postoperative monitoring variables measured by the nurses (HR, RR, SpO2, SAP, DAP, and temperature) during the first 72 postoperative hours at a frequency determined by the medical indications will be collected using Easily software and recorded on a dedicated electronic case report form (eCRF). The time of occurrence of any complications noted by nurses and doctors will also be recorded on the eCRF.

The wearable device transmits the measurement data every 5 minutes to the Biobeat Gateway through Bluetooth. All data are uploaded to and stored on the
Instamed (a French telemedicine company and Biobeat’s partner) certified health data hosting cloud (hosted by Amazon Web Services and General Data Protection Regulation compliant). The research team can then access data through the Instamed platform as well as request that data be exported as.csv files. Nursing staff and doctors will not have access to monitoring data during the protocol duration. The data will be deleted at the end of the study and can be deleted during the study as needed.

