### Outcome measures

The main outcome is the occurrence of one or more episodes with a mean arterial pressure below the threshold of 60 mmHg during the first 72 hours following a major non-cardiac surgical procedure unless death or hospital discharge occurs sooner, with the 72-hour period starting when the patient returns to the surgical department. The secondary outcomes will concern the frequency of postoperative respiratory or temperature abnormalities and their duration, the frequency of artefacts and blank/null outputs from the wearable device and, more globally, the signal-level validity, the postoperative complications that occurred during the monitoring period, as determined by the healthcare team in accordance with the Dindo and Clavien classification
^
12
^ and the comprehensive complication index.
^
13
^ Finally, the ease of use of the device at the time of insertion and the patient’s tolerance to wearing the Biobeat
^®^ device will also be determined. Definitions of hemodynamic, respiratory, and temperature abnormalities are listed in
Table 1.

**Table 1. T1:** Outcome definitions.

Primary Outcome Measure
Postoperative haemodynamic abnormality
• a MAP < 70 mmHg
• or a MAP < 65 mmHg
• or a MAP < 60 mmHg
• or a MAP < 80% of the value measured during the pre-anaesthesia consultation
• or a MAP < 70% of the value measured during the pre-anaesthesia consultation
• or a MAP < 80% of the value measured in the OR before the induction of anaesthesia
• or a MAP < 70% of the MAP measured in the OR before the induction of anaesthesia
• or a MAP > 100 mmHg
• or a MAP > 110 mmHg
• or a MAP > 120 mmHg
• or a MAP > 130 mmHg
• or a MAP > 120% of the MAP measured during the pre-anaesthesia consultation
• or a MAP > 130% of the MAP measured during the pre-anaesthesia consultation
• or a MAP > 120% of the MAP measured in the OR before induction of anaesthesia
• or a MAP > 130% of the MAP measured in the OR before induction of anaesthesia
• or a heart rate < 40/min
• or a heart rate > 100/min
• or a rhythm disorder
Secondary Outcomes
Postoperative respiratory abnormality
• breathing rate < 8/min
• breathing rate > 20/min
• or a peripheral oxygen saturation < 95%
• or a peripheral oxygen saturation ≤ 92%
• or a peripheral oxygen saturation ≤ 90%
• or a peripheral oxygen saturation ≤ 85%
Postoperative temperature abnormality
• a temperature ≤ 36.8°C
• or a temperature ≥ 38°C
• or a temperature ≥ 39°C

MAP: mean arterial pressure; OR.

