## Discussion

Post-operative monitoring of surgical patients as practiced in general wards is not entirely satisfactory due to its intermittent nature. This monitoring is further degraded in case of reduced nursing staff and during night hours with increased patient/staff ratios.
^
16
^ This problem is all the more important as the number of patients at risk for postoperative complications will increase, particularly due to the growing population of elderly subjects.
^
17
^ The possibility of compensating for the lack of monitored beds, whether it is intensive care units and high dependency care units, remote monitoring brings new perspectives. In addition, remote monitoring could be the solution in case of lack of monitored beds.

Leenen
*et al.* recently published a systematic review of the literature reporting the feasibility of the use of 13 devices and their validation for in-hospital continuous vital signs monitoring.
^
18
^ Since this publication, telemonitoring has been studied outside the hospital either in patients who have undergone esophagectomy during the first 7 days at home after discharge
^
19
^ or in patients with COVID-19.
^
9,
20
^ Some points remain to be clarified, notably the frequency of artefacts and false alarms and the clinical consequences of the use of remote monitoring.

Our protocol seeks to specify the frequency of artefacts using both automatic detection with predefined bounds but also with review by clinicians as reported in a study concerning the feasibility of continuous monitoring of vital signs in surgical patients on a general ward using SensiumVitals patch.
^
21
^ This study showed a high percentage of artefacts concerning the respiratory rate measurement (51% of the measurements), and a lower percentage concerning the heart rate measurement (19%) and temperature (9%). This point is crucial as artefacts will generate false alarms leading to the rejection of the technique by caregivers.

We aimed also to measure the gap between the nurse’s observation of an abnormality in a vital parameter and those detected by the remote monitoring. Such an extent will be a strong argument to encourage the generalization of this new type of monitoring, especially as its cost is not yet well known.

This cost has been estimated to be in the order of £400 to £550 per patient in a remote home monitoring model during the COV1D-19 pandemic.
^
20

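### The artefact rules may be updated during the study and re-applied to all recordings, with no freeze point and no version named for the main analysis

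*Protocol article*

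**What the plan says.** The paragraph on detection of artefacts, under Statistics, sets the starting point: "This will follow similar rules as previously published in a paper dedicated to the validation a new sensor". The rules themselves are not listed. It then allows change: "The rules selected to define artefacts may be updated according to experience and the literature". It also says how change is handled: "The successive rules will be recorded in a register, and all recordings will be reviewed in the light of these new rules". No cut-off for updates is stated, and no version is named as the one on which the main result rests.

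The Discussion describes artefact detection as "using both automatic detection with predefined bounds but also with review by clinicians".

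Outcome measures defines the endpoint that the filter acts on: "The main outcome is the occurrence of one or more episodes with a mean arterial pressure below the threshold of 60 mmHg", over the first 72 hours on the ward. No minimum duration of an episode is given. Data collection gives the density of readings: "The wearable device transmits the measurement data every 5 minutes to the Biobeat Gateway through Bluetooth". The same section gives the research team access to the device data and to exports, without a limit on timing. The only masking it states keeps device data from nurses and doctors.

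Statistics compares nurse and device detection per patient in a two-by-two table with a McNemar test. It sizes the study on an expected prevalence of 8%, to be estimated to within 5 points either way.

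**The concern.** An any-event outcome on dense recordings is very sensitive to the filter that decides which low values are real. A loose rule lets isolated false lows turn patients positive, and a strict rule removes true episodes. Here the filter can be revised while the data accumulate, and each revision re-scores data already collected. The text does not say when this stops.

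The protocol also carries expectations about the result. Its stated goal includes corroborating an 8% prevalence, and its hypothesis is that the sensor detects abnormalities more often than nurses do. Rules revised in the light of accumulating results could move the estimate towards either expectation without anyone intending it. Both the prevalence of severe hypotension and the nurse-versus-device comparison would be affected, because the device side of each passes through the same filter.

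Open-ended updating also sits uneasily with the Discussion, which tells the reader that the bounds are set in advance.

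**Working it through.** **Inputs from the document.** Expected prevalence 8%; half-width 5 points; two-sided alpha 5%; N = 114; one transmission every 5 minutes for 72 hours, so at most 72 × 12 = 864 readings per patient.

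**Inputs that are assumed.** The rate q at which a reading falsely shows MAP below 60 mmHg and is not flagged. The document gives no such rate. The artefact shares in its Discussion (51%, 19% and 9%) concern respiratory rate, heart rate and temperature on another patch, so they cannot supply it.

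**The plan's own figure.** n = 1.96² × 0.08 × 0.92 / 0.05² = 113.09, rounded up to 114. It reproduces. The half-width at 114 is 4.98 points. The sample size is not in dispute.

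**Leverage of the filter, independent readings.**
- Chance of at least one unflagged false low in a patient: P = 1 − (1 − q)^864
- Observed proportion with 8% true prevalence: 1 − 0.92 × (1 − P)

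| q per reading | P | Observed proportion |
|---|---|---|
| 1 in 100,000 | 0.9% | 8.8% |
| 5 in 100,000 | 4.2% | 11.9% |
| 1 in 10,000 | 8.3% | 15.6% |
| 2 in 10,000 | 15.9% | 22.6% |
| 5 in 10,000 | 35.1% | 40.3% |

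A shift of 5 points, the whole planned half-width, needs P = 0.05 / 0.92 = 5.43%. That gives q = 1 − (1 − 0.0543)^(1/864) = 0.0000647, about 1 reading in 15,500.

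**Leverage if false lows cluster.** Suppose they fall only in a share s of the non-hypotensive patients. The observed proportion is 0.08 + 0.92 × s:
- s = 1%: 8.9%
- s = 5%: 12.6%
- s = 10%: 17.2%

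**The other direction.** About 0.08 × 114 = 9 events are expected. If a stricter rule reclassifies 3 of them as artefact, the estimate is 6/114 = 5.3%.

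**The comparison with nurses.** Taking the exact form of the McNemar test, 5 discordant patients against 0 give p = 2 × 0.5⁵ = 0.0625, and 6 against 0 give p = 2 × 0.5⁶ = 0.031. In such a case one reclassified patient crosses the 5% level.

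**The case against.** The article has real safeguards. Rule versions are logged, every recording is re-reviewed under the new rules so that patients are treated alike, and no interim analyses are planned. A lock date or reviewer masking may stand in the full protocol, which the article says is available on request. All of this is fair. But the point does not rest on silence: the article itself grants permission to change the rules and re-score, and places no end on it. A register lets a reader see afterwards that the rules moved; it does not stop them moving in response to results.

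It is also true that the link to the main outcome is inferred. Artefact frequency appears as a secondary outcome, and nowhere does the text say that flagged readings are removed before episodes are counted. Exclusion is the natural reading, but it should be named as a reading.

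A reader might infer four stronger things that the document does not support:

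- **That re-review is impossible because data may be deleted.** Data collection does say "The data will be deleted at the end of the study and can be deleted during the study as needed". But that sentence closes a paragraph on the hosting platform, which also provides for export of the data, and Data availability promises deposit in a public repository. At most the wording is loose.
- **That the Discussion flatly contradicts Statistics.** Each rule version can have its bounds set before it is run. This is tension in wording, not contradiction.
- **That the filter can move the result by 27 points.** Comparing 8.3% with 35.1% gives that figure, but these are false positives alone, with no true hypotension. At 8% true prevalence the same rates give 15.6% and 40.3%, a gap of 24.7 points. That gap still depends on assumed rates and independence. With clustering in 1% to 5% of non-hypotensive patients, the shift from 8% is 0.9 to 4.6 points.
- **That rules will be tuned to the study's own recordings, or by reviewers who see the nurse chart.** The text says neither. It leaves both open, which is a risk and not evidence of intent.

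**Conclusion.** The point holds as a weakness in what the plan fixes. The artefact rules may change and be re-applied to all data, with no cut-off and no version named for the main analysis. If flagged readings are excluded, the device-positive proportion and the McNemar comparison are open to data-driven choice.

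The size cannot be known from the document. The calculations show that rare unflagged false lows could use up the planned precision if readings were independent. Real artefacts probably cluster within patients, which makes the effect smaller for the same number of false readings: still material at the upper end of the range shown, and slight at the lower end. These figures show direction and scale; they do not predict the bias. The sample size is unaffected.

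**What to change.** Amend the artefact paragraph under Statistics, or the analysis plan, as follows:

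1. State whether flagged readings are excluded when episodes of MAP below 60 mmHg are counted.
2. Allow rule updates only on the basis of sensor traces, with those who set the rules or review recordings not seeing nurse values or complications.
3. Freeze the rule set before sensor and nurse data are linked, and name that version as the one for the main analysis.
4. Report the main outcome under the initial rules, those taken from the published validation work, as a sensitivity analysis. Treat any change after the freeze as sensitivity analysis only.
5. Align the Discussion's description of the bounds with this process.

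Optionally, clarify that raw exports are kept until analysis is complete.

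The cost is a few sentences and one additional run of the analysis, with no change to the sample size. The drawback is that a genuine improvement in the rules found after the freeze cannot enter the main analysis.

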### Quality control

Quality control is carried out by the Clinical Research Unit of the sponsor hospital. A qualified person will attest subject eligibility, monitor integrity of the source data and completion of the entries on the electronic case report form, verify the compliance with the clinical study protocol, the Good Clinical Practices, and the regulatory commitments). The monitor will also verify the report of adverse effects.

All subjects will be identified by a unique identification number. Each principal investigator will keep a list in a safe location which will allow the identification of the pseudonymised patients. Patients will be informed about data protection and the fact that data passed to other investigators or an authorized party for analysis will occur in a pseudonymised manner. Data analysis by the biostatistician will also be performed in a pseudonymised manner.

## Discussion

Post-operative monitoring of surgical patients as practiced in general wards is not entirely satisfactory due to its intermittent nature. This monitoring is further degraded in case of reduced nursing staff and during night hours with increased patient/staff ratios.
^
16
^ This problem is all the more important as the number of patients at risk for postoperative complications will increase, particularly due to the growing population of elderly subjects.
^
17
^ The possibility of compensating for the lack of monitored beds, whether it is intensive care units and high dependency care units, remote monitoring brings new perspectives. In addition, remote monitoring could be the solution in case of lack of monitored beds.

Leenen
*et al.* recently published a systematic review of the literature reporting the feasibility of the use of 13 devices and their validation for in-hospital continuous vital signs monitoring.
^
18
^ Since this publication, telemonitoring has been studied outside the hospital either in patients who have undergone esophagectomy during the first 7 days at home after discharge
^
19
^ or in patients with COVID-19.
^
9,
20
^ Some points remain to be clarified, notably the frequency of artefacts and false alarms and the clinical consequences of the use of remote monitoring.

Our protocol seeks to specify the frequency of artefacts using both automatic detection with predefined bounds but also with review by clinicians as reported in a study concerning the feasibility of continuous monitoring of vital signs in surgical patients on a general ward using SensiumVitals patch.
^
21
^ This study showed a high percentage of artefacts concerning the respiratory rate measurement (51% of the measurements), and a lower percentage concerning the heart rate measurement (19%) and temperature (9%). This point is crucial as artefacts will generate false alarms leading to the rejection of the technique by caregivers.

We aimed also to measure the gap between the nurse’s observation of an abnormality in a vital parameter and those detected by the remote monitoring. Such an extent will be a strong argument to encourage the generalization of this new type of monitoring, especially as its cost is not yet well known.

This cost has been estimated to be in the order of £400 to £550 per patient in a remote home monitoring model during the COV1D-19 pandemic.
^
20
^ It will have to be weighed against the cost of a complication avoided or recognized and treated earlier.
^
22,
23
^

### Limitations

Our protocol suffers from several weaknesses. The first is that this study will take place during the COVID-19 pandemic, which profoundly changes hospital activity and its functioning. In addition, patients included in the study are at intermediate risk since their procedure will last more than 2 hours and they are expected to have a postoperative stay of more than 72 hours but are not expected to be hospitalized in a monitored unit. This obviously reflects a practice specific to each health facility. We decided not to include in the study patients with very hairy thoracic skin since we decided not to ask patients to shave their chests. This induces a bias in the selection of the patients due to the non-inclusion of some men. We chose to have data registered by the nurses gathered at a frequency determined by medical indications and not by a priori determined intervals. Such choice could be considered as a weakness of the protocol, but we wanted to do a real-life study and consequently to have instructions given to nurses by the medical team which may vary from one patient to another. It is of prime importance to notice that only blood pressure measurement passed validation testing for accuracy
^
10
^ and not the other parameters measured by the Biobeat
^®^ sensor to the best of our knowledge. Although this may be a limitation to this study, we decided to use this device because it received approval from the Food and Drug Administration and European Community regulators. Finally, the number of subjects to be included in the study was based on the results of a previous publication on the occurrence of postoperative hypotension.
^
5
^ There is probably some difference between our population and our nursing monitoring modalities and the corresponding elements of this study.
^
5
^ We probably should have done a prior study to better specify the percentage of patients who had a postoperative hypotension in our center. In any case, including 114 patients will allow us to give a first answer to the interest of remote monitoring.

In conclusion, our protocol is specifically aimed to establish whether there is a benefit of remote monitoring using a multiparameter device in the detection of a postoperative complication resulting in an abnormality of one of the major vital signs. This demonstration would encourage the extension of this type of monitoring to hospitalized medical patients and patients at home, which includes many indications: follow-up after discharge, chronic pathology, or acute but not requiring hospitalization.

## Plans for dissemination of the study outcome

Results of the present protocol will be published in peer-review medical journals.

## Data availability

No underlying data are associated with this article but the data for this work will be publicly available in the Dryad repository keeping all data anonymous.
